## Abstract

Venous thromboembolism (VTE), comprising deep vein thrombosis (DVT) and pulmonary embolism, poses a substantial clinical risk, and the incidence of these thrombotic-related diseases remains high. Anticoagulation aims to prevent thrombus extension and reduce the risk of recurrent events, particularly fatal pulmonary embolism. In EINSTEIN DVT, rivaroxaban was non-inferior to enoxaparin/vitamin K antagonists for the reduction of recurrent VTE, with a similar safety profile and a net clinical benefit. EINSTEIN EXT investigated patients receiving long-term treatment in whom there was no clear decision about continuing or stopping anticoagulation; rivaroxaban was superior to placebo in the reduction of recurrent VTE, showing an acceptable benefit–risk balance. Rivaroxaban has the potential to replace standard therapy, usually parenteral low molecular weight heparin overlapping with and followed by a vitamin K antagonist, for the treatment of acute symptomatic DVT and the secondary prevention of VTE. As the use of rivaroxaban for DVT treatment increases in clinical practice, a fundamental understanding of its clinical benefits in everyday patient care is essential. XALIA (XArelto for Long-term and Initial Anticoagulation in venous thromboembolism) is a multicentre, prospective, non-interventional, observational study investigating the effectiveness and safety of a single-drug approach with rivaroxaban compared with standard therapy in patients with DVT. The study cohort will include approximately 4800 patients (≥18 years old) with objectively confirmed acute DVT who will be treated for a period of ≥3 months. The primary outcomes will be the incidence of treatment-emergent adverse events (primarily major bleeding), symptomatic recurrent venous thromboembolic events and all-cause mortality. Secondary outcomes include: major cardiovascular events; patient-reported treatment satisfaction and adherence; healthcare resource utilization; reasons for drug switching or interruption of treatment; and adverse events. XALIA will follow an international cohort of patients in more than 20 European countries, and others including Israel and Canada. The first patient was enrolled in June 2012, with results expected in 2015. It is anticipated that XALIA will provide important information on the treatment of DVT in a heterogeneous, unselected patient population in a real-world setting and provide important supplementary information to that obtained from the EINSTEIN DVT phase III study.

## Introduction

Acute venous thromboembolism (VTE), which comprises deep vein thrombosis (DVT) and pulmonary embolism (PE), is the third most common cardiovascular disorder [1]. VTE occurs with an incidence of 1–2 cases per 1000 people in the general population and the risk increases with age [2,3]. Treatment of VTE involves an initial phase, in which the key imperative is to prevent thrombus extension, improve acute symptoms and reduce the risk of early PE [4]. The current standard treatment for acute VTE is overlapping anticoagulation with a parenteral agent (such as low molecular weight heparin [LMWH]) and a vitamin K antagonist (VKA) [5]. VKAs may be given over a period of months, years, or even indefinitely, to reduce the risk of recurrent events. Guidelines on the duration of anticoagulant therapy for VTE, including those published by the American College of Chest Physicians (ACCP), recommend at least 3 months’ treatment after a provoked or unprovoked event [5].

Anticoagulation with LMWH is rapid and effective, but the need for daily subcutaneous injections can be challenging. Heparin-induced thrombocytopenia may be a risk with LMWH use, with an incidence of ≤1% in medical and postoperative patients [6]. The limitations of VKAs in routine clinical practice are well documented: treatment with these agents requires regular monitoring to ensure patients remain within the therapeutic range (international normalized ratio 2.0–3.0), and a wide range of drug–drug and drug–food interactions may influence therapeutic levels of anticoagulation. Initial adjustment of VKA dosing in the first weeks of therapy is particularly challenging and in some cases is not easy to achieve [7]. Furthermore, the use of a dual-drug approach with LMWH and VKAs can be both complex and burdensome for patients and healthcare providers.

Direct oral Factor Xa inhibitors, such as apixaban, edoxaban and rivaroxaban, and the direct oral thrombin inhibitor dabigatran, have recently been investigated in phase III clinical trials for the treatment and secondary prevention of DVT and PE [8-15]. Rivaroxaban and apixaban have both been studied as a single-drug approach, whereas edoxaban and dabigatran employed an initial course of parenteral heparin therapy before commencing therapy with the anticoagulant being investigated. Data show that these agents are effective and well tolerated; however, it is not known whether these findings are directly applicable to patients in a real-world setting. As the use of the direct oral anticoagulants in clinical practice increases, a fundamental understanding of their efficacy and safety in patients with VTE treated in routine care is essential. XALIA (XArelto for Long-term and Initial Anticoagulation in venous thromboembolism) will investigate the effectiveness of a single-drug approach with rivaroxaban compared with standard dual-drug therapy with LMWH/VKAs in the real-world treatment of patients with DVT.

### Rivaroxaban

Rivaroxaban is a direct oral Factor Xa inhibitor with a high oral bioavailability (≥80%) [16] and predictable pharmacokinetics and pharmacodynamics [17,18]; these characteristics provide the basis for use of this agent without the need for routine coagulation monitoring. The onset of action of rivaroxaban, i.e. its anti-Factor Xa activity, has been shown to be as fast as that of the LMWH enoxaparin [19]. Peak plasma concentrations of rivaroxaban are achieved within 2–4 hours and it has a mean half-life of approximately 9 hours (5–9 hours in young individuals and 11–13 hours in the elderly) [17,18]. Rivaroxaban is associated with few drug–drug [20-22] or drug–food interactions [23]. However, rivaroxaban doses of 15 mg and 20 mg should be taken with food to maintain high oral bioavailability [23].

XALIA is being conducted in response to a request made by the European Medicines Agency (EMA) to evaluate rivaroxaban for the treatment of acute DVT after the completion of the large phase III EINSTEIN DVT study. The EINSTEIN phase III clinical programme investigated the use of rivaroxaban as a single-drug approach in contrast to the current dual-drug paradigm of enoxaparin/VKAs [8,9]. EINSTEIN DVT was a randomized, open-label, event-driven, non-inferiority trial that investigated the efficacy and safety of oral rivaroxaban (15 mg twice daily for 21 days followed by 20 mg once daily) compared with subcutaneous enoxaparin (1 mg/kg body weight twice daily for at least 5 days) overlapping with and followed by a VKA (warfarin or acenocoumarol, started within 48 hours after randomization), in patients with acute, symptomatic, objectively confirmed proximal DVT without PE. Treatment duration was at the discretion of the attending physician and was planned for 3, 6 or 12 months [8]. In EINSTEIN DVT, rivaroxaban was shown to be non-inferior to enoxaparin/VKA for the reduction of recurrent VTE (Table 1) [8]. Rates of first major or non-major clinically relevant bleeding (the primary safety outcome) were similar in patients receiving rivaroxaban compared with patients receiving enoxaparin/VKA. In addition, rivaroxaban was associated with a significantly improved net clinical benefit (defined as the composite of symptomatic, recurrent VTE and major bleeding), compared with enoxaparin/VKA (Table 1) [8]. The consideration of patient-reported outcomes is becoming increasingly important when evaluating the overall effectiveness of direct oral anticoagulants. It is worth noting that an EINSTEIN DVT subanalysis showed that rivaroxaban was associated with improved treatment satisfaction compared with enoxaparin/VKA therapy in patients with DVT [24]. Among the factors noted were a reduction in patient-reported anticoagulation burden and an increase in convenience [24]. It would, therefore, be desirable to confirm the influence of rivaroxaban treatment on patient lives in routine care.

**Table 1 T1:** Efficacy and safety outcomes of the phase III EINSTEIN DVT study

	**Rivaroxaban**	**Enoxaparin/VKA**	**HR (95% ****CI)**	**P value**
**Efficacy outcomes (ITT population)**	(n = 1731)	(n = 1718)		
Recurrent VTE* (%)	2.1	3.0	0.68 (0.44–1.04)	<0.001
**Safety outcomes (safety population)**	(n = 1718)	(n = 1711)		
First major or non-major clinically relevant bleeding^†^ (%)	8.1	8.1	0.97 (0.76–1.22)	0.77
Major bleeding (%)	0.8	1.2	0.65 (0.33–1.30)	0.21
Non-major clinically relevant bleeding (%)	7.3	7.0		
Total mortality (%)	2.2	2.9	0.67 (0.44–1.02)	0.06
Any treatment-emergent adverse event (%)	62.7	63.1		
**Net clinical benefit**	2.9	4.2	0.67 (0.47–0.95)	0.03
**(composite of symptomatic, recurrent VTE plus major bleeding, %)**				

*Primary efficacy outcome; ^†^principal safety outcome.

CI, confidence interval; DVT, deep vein thrombosis; HR, hazard ratio; ITT, intention to treat; PE, pulmonary embolism; VKA, vitamin K antagonist; VTE, venous thromboembolism.

The EINSTEIN PE study investigated rivaroxaban in patients with acute, symptomatic PE, and also showed that it was non-inferior to enoxaparin/VKA, with a 51% reduction in the incidence of major bleeding [9]. The EINSTEIN EXT study investigated rivaroxaban in patients receiving long-term treatment in whom there was no clear decision about continuing or stopping anticoagulation; rivaroxaban was superior to placebo in the reduction of recurrent VTE, and showed an acceptable benefit–risk balance [8].

Rivaroxaban is the first direct oral anticoagulant to be approved for the treatment of DVT and PE and secondary prevention of VTE in the European Union, US and Canada. XALIA is a multicentre, prospective, non-interventional, observational study taking place across more than 20 European countries, and other countries including Israel and Canada. XALIA will assess whether the results obtained with rivaroxaban in real-world clinical practice in patients with objectively confirmed, acute DVT and an indication to receive anticoagulation for at least 3 months are consistent with those seen in the phase III EINSTEIN DVT study.

The main objective of the study is to evaluate the safety of rivaroxaban in routine clinical practice for the treatment of acute symptomatic DVT and prevention of recurrent VTE by examining the incidence of treatment-emergent adverse events: major bleeding, symptomatic recurrent venous thromboembolic events and all-cause mortality.

## XALIA study design

The study cohort consists of patients with acute DVT treated with rivaroxaban or current standard therapy (initial treatment with unfractionated heparin, LMWH or fondaparinux, which may overlap with and be followed by an oral VKA) for a period of ≥3 months. The study duration will be 12 months from the final date of patient enrolment, but the treatment duration for each patient will be determined solely by the attending physician and does not depend on the initial intended treatment duration or the study duration. The first patient was enrolled in June 2012 and the end of study is expected in 2015.

### Administrative organization

Non-interventional post-authorization safety studies are recommended for review by Ethics Committees, and the study/sponsor sought approval from an independent Ethics Committee or Institutional Review Board in all countries where such procedures were in place.

An external expert scientific Steering Committee will give support regarding study objectives, study conduct and analysis. An independent Adjudication Committee blinded to the treatment group will adjudicate events. Members of the Steering Committee may also serve on the Adjudication Committee; however, no sponsor representatives will serve on the Adjudication Committee. The study is registered at clinicaltrials.gov (NCT01619007).

### Centre and patient selection

Recruitment of patients will be conducted by investigators at selected study centres in Europe and other regions in which rivaroxaban is approved. Enrolment is planned for approximately 4800 patients with approximately equal numbers in each arm. Patients can be enrolled immediately after a decision about the choice of anticoagulant therapy has been made, but no randomization will be undertaken. Inclusion and exclusion criteria are summarized in Table 2.

**Table 2 T2:** Inclusion and exclusion criteria for XALIA

**Inclusion**	**Exclusion**
● Female or male patients who are ≥18 years of age	● Patients with acute symptomatic PE*
● Diagnosis of acute DVT, objectively confirmed	● Other exclusion criteria are dependent on local product information
● Indication for anticoagulation therapy for at least 12 weeks	
● Patients willing to participate in the study and available for follow-up	

*A parallel symptomatic PE is not an exclusion criterion; however, XALIA will not enrol patients with only PE.

DVT, deep vein thrombosis; PE, pulmonary embolism.

Patients who are ≥18 years old, with a diagnosis of objectively confirmed, acute DVT and an indication to receive anticoagulation for ≥3 months will be included. If anticoagulation is administered for a shorter period than planned, patients will remain in the study.

### Study outcomes

Primary study outcomes are the incidence of treatment-emergent adverse events, namely major bleeding, symptomatic recurrent venous thromboembolic events and all-cause mortality. Major bleeding is defined as overt bleeding associated with a fall in haemoglobin of ≥2 g/dl; or a transfusion of ≥2 units of packed red blood cells or whole blood; or bleeding at a critical site (intracranial, intraspinal, intraocular, pericardial, intra-articular, intramuscular with compartment syndrome, retroperitoneal); or death. Secondary outcomes include: major cardiovascular events; patient-reported treatment satisfaction and adherence; healthcare resource utilization; reasons for drug switching or interruption of treatment; and adverse events, including serious adverse events. Data on patients with renal impairment treated for acute DVT within the terms of the local product information will also be collected and analysed. The Adjudication Committee, blinded to the treatment group, will adjudicate bleeding events; recurrent VTE and other thromboembolic events; major cardiovascular events; and cause of death. Local objective diagnosis of symptomatic recurrent venous thromboembolic events is a prespecified criterion for event adjudication.

### Drug administration

The type, dose and duration of drug therapy are at the sole discretion of the attending physician. Enrolment will only be considered after the treatment decision has been made. Patients who commence treatment with rivaroxaban, or those who initially receive treatment with heparin/fondaparinux within 48 hours of enrolment, can be included in the rivaroxaban cohort. Patients in the standard-of-care cohort are those receiving other recommended pharmacological treatments for VTE according to international guidelines, e.g. initial unfractionated heparin, LMWH or fondaparinux, which may overlap with and be followed by an oral VKA. However, in routine clinical practice many patients for whom rivaroxaban is planned may initially receive parenteral anticoagulants for a period longer than 48 hours before they are switched to rivaroxaban. These patients will be excluded from the main analysis, but the allocation of these patients will be subject to sensitivity tests as follows: 1) they will be analysed separately and 2) they will be allocated to standard of care or rivaroxaban dependent on the distribution of days (after the first 48 hours) in which they actually switched to rivaroxaban; the cut-off points that will be used for these sensitivity analyses will be defined by the quartiles of the distribution of days (after the 48 hours) in which the switch occurs.

Concomitant medications taken prior to or during the study will be documented and include non-steroidal anti-inflammatory drugs, acetylsalicylic acid, clopidogrel, steroids, medications known to interact with the DVT treatment, and medications known to increase or reduce the incidence of DVT (e.g. hormone therapy). Other drugs will be recorded if considered medically relevant by the investigator. Any changes to VTE treatment, including switching or cessation of treatment, will be documented.

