### Statistical analysis

The primary statistical analysis includes a descriptive analysis of the primary and secondary outcomes. The primary outcome variable is the incidence of treatment-emergent adverse events, namely major bleeding and symptomatic recurrent VTE. An adverse event is considered as treatment emergent if it starts on or after the day of the first dose of study medication and ≤2 days after the last dose. All patients who took at least one dose of medication will be included in the safety population. For primary and secondary variables, incidence proportions and incidence rates will be estimated, together with 95% confidence intervals. The accepted range for the 95% confidence intervals is estimated to be between the allocation ratios of 1:3 and 3:1; therefore, at least 25% of patients at each study centre should receive either standard of care or rivaroxaban therapy. To compare the treatment arms, the risk difference and corresponding 95% confidence interval will be calculated, and time-to-event analyses will be conducted.

The potential for allocation bias in open-label, non-randomized studies will be minimized by also presenting a propensity score analysis to control the effect of unbalanced covariates [26,27]. To minimize selection bias, physicians will be asked to document patients consecutively. To decrease the possibility of reporting bias, source data will be verified at approximately 10% of study centres in countries where this is legally possible. A sample size of 4800 patients assumes that 17% of patients will be non-evaluable because of non-overlapping propensity scores or because of withdrawn informed consent forms.

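### The main analysis drops patients planned for rivaroxaban according to what happens after enrolment, and the quartile re-allocation cannot test what that does

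*Protocol article*

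**What the plan says.** The order of events is clear. Drug administration states: "Enrolment will only be considered after the treatment decision has been made". Centre and patient selection agrees, so the intended anticoagulant is known when the patient enters.

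Drug administration then expects that "many patients for whom rivaroxaban is planned may initially receive parenteral anticoagulants for a period longer than 48 hours before they are switched to rivaroxaban". It gives no proportion. Their handling is: "These patients will be excluded from the main analysis, but the allocation of these patients will be subject to sensitivity tests as follows". Two tests follow:

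- First, "they will be analysed separately".
- Second, "they will be allocated to standard of care or rivaroxaban dependent on the distribution of days". The days meant are those from the 48-hour limit to the observed switch, and the cut-offs are "defined by the quartiles of the distribution of days (after the 48 hours) in which the switch occurs".

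The same section describes the standard-of-care cohort as patients receiving other recommended treatments, for example initial heparin, LMWH or fondaparinux. A VKA may follow but is not required.

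The 48 hours appears in two forms. The sentence admitting patients to the rivaroxaban cohort ties initial heparin or fondaparinux to a window of 48 hours around enrolment. The sentence describing the excluded group refers to how long parenteral treatment lasted before the switch.

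**The concern.** Whether a patient planned for rivaroxaban belongs to the main analysis depends on heparin duration and switching, both of which are observed after enrolment. Consider a patient planned for rivaroxaban who dies on heparin on day 5. That patient never becomes a switcher and, as treated, resembles the standard-of-care description. The same patient without the event switches and is excluded. No sentence says which cohort, if any, holds the first patient. A propensity score built on baseline covariates cannot correct a selection rule that operates after baseline.

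The second sensitivity analysis does not examine this. Everyone with an observed switch day was followed to that day, and the whole patient is then placed in one arm. The receiving arm therefore gains heparin time in which, for a fatal event, nothing could have been recorded. Because the cut-offs are quartiles of the observed switch days, they are also unknown until the data are in.

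At stake is the between-arm contrast for major bleeding, recurrent VTE and death in the first weeks of treatment.

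**Working it through.** The article gives no figure for this point, so there is nothing to reproduce. The check asks how far each reading of the rule moves the RR (rivaroxaban versus standard of care) when the true RR is 1 and there is no confounding.

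**Inputs**

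- From the article: about 4800 patients in roughly equal arms. Reference one-year risks are set at 1.2% and 3.0%, the enoxaparin/VKA figures for major bleeding and recurrent VTE in Table 1.
- Assumed, with ranges: share *f* of rivaroxaban-planned patients with more than 48 hours of heparin, 10%, 20% or 40%; share *e* of one-year events in the first 21 days, 10%, 33% or 50%; switch day uniform on days 3 to 14 (mean 8.5).

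**Formula.** Daily early risk is λ = *eR*/21. Counts are fractions of all enrolled patients: 0.5 standard of care, 0.5(1−*f*) rivaroxaban without long lead-in, 0.5*f* with it.

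**Main analysis, extreme inputs** (*R* = 0.03, *e* = 0.5, *f* = 0.4)

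1. λ = 0.5 × 0.03/21 = 0.000714. Pre-switch risk = 8.5 × 0.000714 = 0.00607.
2. Pre-switch events = 0.2 × 0.00607 = 0.001214, which is 5.8 patients in 4800.
3. If these count as standard of care: (0.015 + 0.001214)/(0.5 + 0.001214) = 0.03235. RR = 0.0300/0.03235 = **0.927**.
4. At the mild end (*e* = 0.1, *f* = 0.1): λ = 0.000143 and pre-switch events = 0.05 × 8.5 × 0.000143 = 0.0000607. RR = 0.0300/[(0.015 + 0.0000607)/(0.5 + 0.0000607)] = **0.996**.
5. If every rivaroxaban-planned patient with long lead-in is removed, switched or not, neither arm's risk changes and RR = **1.00**.

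Steps 3 and 5 treat events in the first 48 hours like later pre-switch events. If the first-48-hour events stay in the rivaroxaban cohort instead (0.2 × 2 × 0.000714 = 0.000286), its risk is (0.009 + 0.000286)/(0.3 + 0.000286) = 0.03092. Standard of care with the remaining events is (0.015 + 0.000929)/(0.5 + 0.000929) = 0.03180. Step 3 becomes 0.03092/0.03180 = 0.972, and step 5 becomes 0.03092/0.0300 = 1.03.

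**Second sensitivity analysis, same extreme inputs**

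- *Cut at the third quartile, pre-switch events in standard of care.* Switchers on days 3–11 (mean 7) go to rivaroxaban: (0.009 + 0.15 × (0.03 − 0.005))/(0.3 + 0.15 × 0.995) = 0.02838. Those on days 12–14 (mean 13) go to standard of care: (0.015 + 0.001214 + 0.05 × (0.03 − 0.00929))/(0.5 + 0.001214 + 0.05 × 0.9907) = 0.03132. RR = **0.906**.
- *Cut at the first quartile, pre-switch events dropped.* Days 3–5 (mean 4) go to rivaroxaban: (0.009 + 0.05 × (0.03 − 0.00286))/(0.3 + 0.05 × 0.9971) = 0.02960. Days 6–14 (mean 10) go to standard of care: (0.015 + 0.15 × (0.03 − 0.00714))/(0.5 + 0.15 × 0.9929) = 0.02840. RR = **1.042**.

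The full grid, with exponential rather than linear risk, gives:

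| Pre-switch events | Main analysis | Q1 cut | Median cut | Q3 cut |
|---|---|---|---|---|
| Counted as standard of care | 0.93–0.996 | 0.98–0.999 | 0.95–0.997 | 0.90–0.995 |
| Excluded or dropped | 1.00 | 1.003–1.043 | 1.001–1.013 | 0.97–0.999 |

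Grouping by drug planned at enrolment, with follow-up from enrolment, returns 1.00 by construction.

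**The case against.** A reader might infer a predictable immortal-time bias in favour of rivaroxaban. The article does not support that. It requires pre-switch events to be counted as standard of care, which no sentence states. The excluded group is described by the plan for rivaroxaban, and standard of care as other treatments, so excluding such a patient is an equally fair reading. With pre-switch events dropped, the second sensitivity analysis moves against rivaroxaban at the first-quartile and median cuts, because late switchers carry event-free time into standard of care. Larger shifts could be obtained by sending every switcher to rivaroxaban, but quartile cut-offs do not do that. In the main analysis the patients are removed, so the defect there is selection. Misassigned event-free time belongs mainly to the second sensitivity analysis.

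A reader might also see a conflict with the Statistical analysis section: "All patients who took at least one dose of medication will be included in the safety population". It is not one. A safety population of everyone dosed can contain a narrower main comparison, and the separate analysis of switchers needs them in it.

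Other points carry weight. The article names the group openly, analyses it separately and varies its allocation. Its primary analysis is descriptive. Excluding long heparin lead-in fits a single-drug question. The shift is also small beside random error: with 2400 planned per arm, a 3% risk and 20% excluded, 72 versus 57.6 events give a 95% confidence factor of exp(1.96 × √(1/72 + 1/57.6)) = 1.41 either way.

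This settles direction and size. It leaves the structure as it was: membership turns on later events, the home of pre-switch events is not stated, and the planned test cannot reveal the effect. Random error does not excuse a systematic shift that can be removed cheaply.

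**Conclusion.** The concern holds as a matter of structure, without a fixed direction. The main analysis selects on post-enrolment heparin duration and switching although the planned drug is known, and the second sensitivity analysis misassigns pre-switch time at data-derived cut-offs.

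With a true RR of 1, the main RR is about 0.93 to 1.00 if pre-switch events count as standard of care and 1.00 if all such patients are excluded. The second sensitivity analysis runs from about 0.90 to 1.04. The ends of these ranges need 40% long lead-in and half of the events within 21 days. These inputs are assumptions, as are the uniform switch days and the absence of confounding. The 1.00 also assumes that events do not alter heparin duration and that first-48-hour events are not kept selectively in one cohort.

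The two wordings of the 48-hour limit are a separate, smaller defect. A patient who starts heparin at enrolment and continues for a week fits both the inclusion and the exclusion sentence.

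**What to change.** - Keep the single-drug main analysis, but exclude rivaroxaban-planned patients with more than 48 hours of parenteral treatment whether or not they later switch. Never count their pre-switch events in the standard-of-care cohort, and state how events within the first 48 hours are assigned.
- Add a prespecified analysis by drug planned at enrolment, with one common start of follow-up in both cohorts. It should accompany the main analysis, since replacing it would change the question from single-drug to planned treatment.
- Replace the quartile re-allocation with a time-updated exposure analysis: person-time and events belong to parenteral treatment until the switch and to rivaroxaban afterwards. Run it on the time-since-start scale, so that early high-hazard time is compared with early time.
- Keep the separate analysis of early switchers.
- Reconcile the two 48-hour statements to one anchor.

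Cost: changes to protocol and analysis-plan wording, a little more analysis work, and one case-report field for the planned drug if it is not already captured. Treatment changes and switches are already documented. The planned-drug contrast includes some heparin exposure and is slightly diluted. None of this removes confounding, which remains the task of the propensity score.
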